6.3.8.1 Height

Height will be recorded on CRFs at entry using the instructions found in the Adult AIDS Clinical Trials Group Metabolic webpage <http://aactg.s-3.com/members/download/other/metabolic/H&Wmeasures.doc>

- - - 1. Weight

Weight will be recorded on CRFs at screening and at each main study visits using instructions found in the Adult AIDS Clinical Trials Group Metabolic webpage <http://aactg.s-3.com/members/download/other/metabolic/H&Wmeasures.doc>

- - - 1. Resting Blood Pressure

Blood pressure measurements will be recorded on the CRFs at screening and at each main study visits. Blood pressure measurements should be obtained prior to the brachial artery ultrasound measurements.

Blood pressure measurements should be performed manually using an anaeroid sphygmomanometer on the same arm throughout the study. The subject should first sit quietly for five minutes. With the elbow and forearm resting comfortably on a flat table, the blood pressure should then be measured. After two minutes, repeat blood pressure measurement in the same arm. After another two minutes, repeat blood pressure measurements again. Therefore, three blood pressure measurements are to be documented in the CRFs at each main study visit.

- - - 1. Resting Heartrate

Resting heartrate measurements will be recorded on the CRFs at each main study visit. Heartrate measurements should be obtained prior to the brachial artery ultrasound measurements. Heartrates should be measured manually over the entire 60-second period. This may be done prior to the first blood pressure measurement. The subject should first sit quietly for five minutes.

- - - 1. Waist and Hip Measurements

Waist and hip circumferences will be measured at the time of each main study visit and recorded in the CRFs. These measurements will be made in triplicate according to the instructions found in the Adult AIDS Clinical Trials Group Metabolic webpage <http://aactg.s-3.com/members/download/other/metabolic/CIRCmeasures.doc>

- - - 1. Brief Physical Examination

The following assessments will be performed at screening:

- Auscultation of heart for signs of cardiac arrhythmias and valvular murmurs
- Auscultation of carotid arteries for bruits

The following assessments will be performed at each main study visit:

- Examination of the heart for arrhythmias
- Auscultation of the skin for rash or jaundice
  - Query of subject to ascertain whether s/he has experienced symptoms typically associated with pentoxifylline (abdominal discomfort, belching/flatus/bloating, dyspepsia, nausea/vomiting, flushing, dizziness, blurred vision)

These evaluations will be supplemented by additional features based on signs or symptoms that the subject experienced since the last study visit. All findings will be recorded on CRFs at screening or at each main study visit.

- - - 1. Signs and Symptoms

All signs and symptoms must be documented in the subject’s record. All signs and symptoms occurring within 30 days of entry and/or since the last study visit, regardless of grade, must be recorded on CRFs.

6.3.8.8 Diagnoses

All confirmed and probable diagnoses made since the last visit will be recorded on the CRFs, including current status at the time of the study visit.

6.3.8.9 Adherence Assessments

Subjects will be asked to bring their pill bottles with them at each visit so that a pill count can be estimates. They will also be asked to state how many doses of pentoxifylline were taken over the three days prior to the study visit. This information will be recorded on the CRFs.

6.3.8.10 Assessment of Successful Blinding

Once all study procedures have been completed, at the closeout visit each participant will be asked if s/he believed that each had received either pentoxifylline vs. placebo. The study nurse for each participant will also be asked this question. Answers will be recorded on CRFs for batched analysis at the end of the entire trial to assess the success of the blinding strategies for this trial.

6.3.8.11 Laboratory Evaluations

All screening and main study visit laboratory evaluations performed as part of this study must be present in source documentation. At entry, record all laboratory values on CRFs. For post-entry assessments, record on CRFs all Grade ≥ 2 laboratory toxicities and any laboratory toxicities that led to a change in pentoxifylline dosing regardless of grade. In addition, record on CRFs all values for hemoglobin, serum creatinine/calculated creatinine clearance, liver function tests, urine analysis, urine pregnancy tests, hepatitis B and C serologies, CD4/CD8 cell counts, and HIV-1 RNA levels. Refer to the Division of AIDS Table for Grading Adult Adverse Experiences on the Regulatory Compliance Center Web page: <http://rcc.tech-res-intl.com/>

Screening visit and main study visit safety blood and urine laboratories will be sent to the Indiana University clinical laboratory for immediate processing and analysis; results will be entered on CRFs and forwarded to the Biostatistical Division for electronic storage. Frozen plasma, serum, and urine specimens for future use will be batch analyzed by the IU clinical laboratory or by Searchlight/Endogen Laboratories; these data will be electronically forwarded to the Biostatistical Division. Serum, plasma, and urine specimens will be processed, stored, and shipped to the Data Coordinating Center for the RFA funding this trial. Brachial ultrasound results will be entered on CRFs and sent to the Biostatistical Division. Computer labels will be generated and affixed to the appropriate specimen containers or brachial ultrasound discs and will include the specimen number, subject number, specimen date, and primary specimen type. Labels must be affixed prior to freezing the vials. Specimen collection, processing, and storage instructions are listed under section 6.3.8.12.

NOTE: The peripheral IV heplock used for both drawing blood samples and for infusion of fluids if necessary during the BART procedure should be placed on an extremity other than the arm used for the brachial artery measurements.

Hematology

- Hemoglobin
- White blood cell count (WBC)
- Differential WBC
- Absolute neutrophil count (ANC)
- Platelets

Liver function tests

- ALT (SGPT)
- AST (SGOT)
- Total bilirubin

Blood Chemistries

- Serum creatinine/estimated creatinine clearance
- Serum glucose, potassium
- Hepatitis B surface antigen, hepatitis B surface antibody, hepatitis B core IgM antibody
- Hepatitis C antibody

Urine Specimen

- Urine analysis (record pH, WBC, RBC, Hgb, protein, leukocyte esterase, nitrite)
- Urine pregnancy test

CD4/CD8 cell counts and percentages

Because of the diurnal variation in CD4 and CD8 cell counts, determinations for individual subjects should be obtained consistently in ether the morning or the afternoon throughout the study, if possible.

Each time a CD4/CD8 cell count measurement is obtained, a WBC and differential from a sample obtained at the same time must also be performed.

HIV-1 RNA Levels

- Roche Amplicor 2.0 PCR viral loads through the IU commercial laboratory

Activated CD8 Cell Measurements

Fresh whole blood collected in K3 EDTA VACUTAINER (lavender) tubes will be transported within two hours of collection to the laboratory of [name] at the Roudebush VA Hospital for advanced flow cytometry measurements to determine the proportion of activated CD8 cells for each subject.

6.3.8.12 Specimen Collection, Processing, Labeling, and Storage for Specimens for Future Analysis

Plasma

- Collection:
  - For plasma #1, collect ONE (1) 7.0-mL, purple-top EDTA tube, FILL COMPLETELY (for possible additional HIV-1 RNA PCR testing). Complete processing within 6 hours of collection.
  - For plasma #2, collect ONE (1) 7.0-mL, purple-top EDTA tube, FILL COMPLETELY. After collection of blood, gently invert the tube 10 to 15 times and keep upright at room temperature until centrifugation. Keep refrigerated at 4oC after draw if unable to centrifuge immediately.
  - For plasma #3, collect an additional ONE (1) 7.0-ml 3.2% buffered Sodium citrate (SCI) tubes, fill completely (for storage). Mix gently by inverting 8 times immediately after filling. Do not shake the tube as this will break down fibrinogen in the sample. COMPLETE PROCESSING W/IN 1 HR OF COLLECTION.
- Processing:
  - For plasma #1 tube, spin at 800 x *g* for 10 minutes at room temperature. Plasma should be carefully removed from each tube, placed in a sterile polypropylene conical centrifuge tube and centrifuged again (at 800 x *g*) at room temperature for 10 minutes to completely remove platelets and cell debris. Prepare at least 3 aliquots (each containing 1.0-mL) from each 7mL EDTA tube and freeze at -80°C.
  - For plasma #2 tube, spin 3000 x *g* for 10 minutes at 4oC. Prepare at least 3 total aliquots containing at least 1.0-mL of plasma each and freeze at 80C within 4 hours of collection.
  - For plasma #3 tube, spin at 1500 x *g* for 15 minutes at room temperature. Prepare at least 3 total aliquots containing at least 1.0-ml of plasma each and freeze at –80ºC within 60 minutes of collection.
- Labeling: Label on each aliquot the protocol-subject number, date, specimen type “HIV-PLA”, “E-PLA”, and “S-PLA” for tube number 1, 2, and 3, respectively.

Serum

- Collection: Collect FOUR (4) 7.0-mL red-top tubes without additive (for glucose, insulin, lipids, inflammatory markers, pentoxifylline levels, and other future studies) at room temperature. Let blood clot 30 minutes at room temperature in vertical position.
- Processing:
  - Spin tubes 10 minutes at 1300 x *g* to separate serum within 1 hour of collection. Prepare at least ten total aliquots containing at least 1.0-mL of serum. Separated serum MUST be refrigerated until frozen. Freeze at -80ºC as soon as possible within 8 hours of collection. Refrigerate aliquots if freezing cannot be accomplished immediately after processing.
- Labeling: Label on each aliquot the protocol-subject number, date, and specimen type “SER”

# Urine

# Collection: Collect at least 15 mL of urine in a standard collection cup using clean catch technique.

# Processing: Prepare at least 4 total aliquots containing at least 2.0-mL in screw-top plastic vials and freeze at ­­‑80ºC.

# Labeling: Label on each aliquot the protocol-subject number, date, and specimen type “URI”

6.3.8.13 Brachial artery ultrasound measurements

All brachial artery ultrasound measurements must be recorded on CRFs. If any of the systolic blood pressures measured on either of the main study visits prior to brachial artery ultrasound measurements is <90mm Hg, then the visit must be rescheduled.

Perform the assessment in the morning to avoid adrenergic stimulation after an overnight fast (approximately 8 hours).

Subjects may not use tobacco-containing products or eat or drink anything other than water for 8 hours prior to the assessment and until it is completed. See section 3.4 for the ultrasound procedure.

1. ADVERSE EVENT MANAGEMENT

The management guidelines listed here are for the adverse events most likely to occur during this protocol. Grade III or IV abnormalities (defined using the Division of AIDS Table for Grading Adult Adverse Experiences) will prompt immediate discontinuation of the drug. For all toxicities that requires pentoxifylline to be permanently discontinued, relevant clinical and laboratory tests will be repeated as needed until there is final resolution or stabilization of the toxicity. Clinical management decisions will be made by the principal investigator in conjunction with the subject’s primary caregiver; care plans and outcomes must be included in the source documentation. Serious adverse events (SAEs) will be documented on CRFs and forwarded to the Indiana University IRB within 10 working days of the event.

7.1 Grade 1 or 2 Toxicity/Adverse Event

Subjects who develop a Grade 1 or 2 adverse event or toxicity (with the exception of drop in hemoglobin/bleeding, rise in LFTs, rise in serum creatinine/decrease in creatinine clearance, rash, and hypotension as addressed below) may continue on protocol. Subjects experiencing Grade 1 or 2 adverse events who choose to discontinue permanently PTX treatment should be encouraged to complete the premature treatment discontinuation evaluations.

7.2 Grade 3 or 4 Toxicity/Adverse Event

Subjects who develop a Grade 3 or 4 adverse event or toxicity will have PTX permanently discontinued. However, if the primary investigator or primary caregiver has compelling evidence that the adverse event is NOT due to PTX, dosing may continue. Subjects experiencing Grade 3 or 4 adverse events who choose to discontinue permanently pentoxifylline treatment should be followed weekly until resolution of the adverse event.

7.3 Pentoxifylline (PTX)

7.3.1 Drop in Hemoglobin/Bleeding Episode

Subjects must be educated about the possible occurrence of anemia and bleeding, including abdominal pain, hematochezia, melena, and sudden onset headache. If these symptoms/signs occur, then a hemoglobin level must be checked. A 2gm/dL or greater drop from baseline in hemoglobin or bleeding episode from any site will result in permanent discontinuation of PTX. However, if the primary investigator or primary caregiver has compelling evidence that the drop in hemoglobin or bleeding episode is NOT due to PTX (e.g. trauma), dosing may continue with no more than a one week hiatus at the discretion of the primary investigator or primary caregiver. Rescheduling of a main study visit, if necessary, will be at the discretion of the primary investigator.

7.3.2 Rise in Liver Function Tests

Subjects must be educated about the possible occurrence of hepatitis and its manifestations, including abdominal pain, nausea, vomiting, and jaundice. If these symptoms/signs occur, then liver function tests must be obtained. If a Grade 3 or 4 toxicity for ALT, AST, or total bilirubin is found either when obtained for symptoms occurrence or at the Week 4 visit, then PTX will be permanently discontinued. However, if the primary investigator or primary caregiver has compelling evidence that the rise in serum ALT is NOT due to PTX, dosing may continue with no more than a one week hiatus at the discretion of the primary investigator or primary caregiver. Rescheduling of a main study visit, if necessary, will be at the discretion of the primary investigator.

7.3.3 Elevation of Serum Creatinine/Decrease in Calculated Creatinine Clearance

A decline in calculated creatinine clearance of > 25mL/min compared with the entry value or to an absolute value < 50mL/min that is confirmed (within one week of the original finding) and is not found to be reversible will result in permanent discontinuation of PTX. A urine analysis and CBC with differential should be obtained with the follow-up serum creatinine testing to assess for the possibility of nephritis (e.g. increase in urine WBCs and/or eosinophilia). However, if the primary investigator or primary caregiver has compelling evidence that the rise in serum ALT is NOT due to PTX (e.g. volume depletion/dehydration), dosing may continue with no more than a one week hiatus at the discretion of the primary investigator or primary caregiver. Rescheduling of a main study visit, if necessary, will be at the discretion of the primary investigator.

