7.3.4 Rash

For a Grade 1 rash, management of PTX is at the discretion of the principal investigator and the primary caregiver.

For a Grade 2 rash, the principal investigator and primary caregiver will hold PTX until rash is resolved. At that time, the subject can be rechallenged at the same PTX dose. However, if the primary investigator or primary caregiver has compelling evidence that the rash is NOT due to PTX (e.g. sunburn), dosing may continue with no more than a one week hiatus at the discretion of the primary investigator or primary caregiver. Rescheduling of a main study visit, if necessary, will be at the discretion of the primary investigator.

If a Grade 2 rash recurs within one week, or if a Grade 3 or 4 rash occurs at any time, then PTX will be permanently discontinued.

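### The exception to the creatinine-clearance stopping rule in 7.3.3 names serum ALT instead of the renal measure that triggers it

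*Combined protocol and SAP*

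**What the plan says.** Section 7.3.3 deals with kidney function. Its trigger is "A decline in calculated creatinine clearance of > 25mL/min compared with the entry value or to an absolute value < 50mL/min". The fall must be confirmed within one week, and if it "is not found to be reversible will result in permanent discontinuation of PTX". The follow-up is also renal: repeat serum creatinine, with urine analysis and a blood count to look for nephritis.

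The exception comes next. The primary investigator or the primary caregiver may let dosing continue, with a pause of at most one week, on compelling evidence that "the rise in serum ALT is NOT due to PTX (e.g. volume depletion/dehydration), dosing may continue".

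The preceding section, 7.3.2, covers liver tests. Its trigger reads "If a Grade 3 or 4 toxicity for ALT, AST, or total bilirubin is found", and its exception applies when either clinician "has compelling evidence that the rise in serum ALT is NOT due to PTX, dosing may continue".

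**The concern.** A stopping rule and its exception should turn on the same finding. In 7.3.3 they do not: the rule turns on creatinine clearance and the exception on ALT. Taken literally, this has two consequences.

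- A participant whose renal decline has a clear cause other than PTX, and whose ALT has not risen, cannot use the exception. There is no ALT rise to attribute, so drug must be stopped permanently or staff must depart from the written text.
- A participant with a renal decline and a coincidental ALT rise of known other cause would meet the written condition, although it says nothing about the kidney. Hepatitis B or C co-infection is not exclusionary under 4.2, so an ALT rise unrelated to drug is conceivable in this population.

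The clause governs permanent discontinuation of blinded study drug. Serum creatinine and calculated clearance are measured at every main study visit (6.1), so the rule will be checked routinely. Section 2.4.2 describes excretion as almost wholly urinary and notes that pharmacokinetics have not been studied in renal dysfunction, so a renal stopping rule has a real purpose here.

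**Working it through.** No arithmetic applies beyond a count. The check sets each trigger in 7.3 beside its exception and then looks for any other text that would supply the right condition.

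**Trigger against exception**

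| Section | Trigger for stopping or holding PTX | What the exception says must not be due to PTX | Within its own trigger? |
| --- | --- | --- | --- |
| 7.3.1 | Hemoglobin drop of 2 g/dL or more, or bleeding | Hemoglobin drop or bleeding | Yes |
| 7.3.2 | Grade 3 or 4 ALT, AST or total bilirubin | ALT rise | Yes, though only one of three tests |
| 7.3.3 | Fall in calculated creatinine clearance | ALT rise | No |
| 7.3.4 | Grade 2 rash | Rash | Yes |
| 7.3.5, 7.3.6 | Gastrointestinal or neurologic symptoms judged likely due to PTX | No such exception, because attribution is in the trigger | Not applicable |

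The wording of the two unaffected neighbours confirms the pattern. In 7.3.1 the clinician "has compelling evidence that the drop in hemoglobin or bleeding episode is NOT due to PTX (e.g. trauma), dosing may continue"; in 7.3.4 the clinician "has compelling evidence that the rash is NOT due to PTX (e.g. sunburn), dosing may continue". Each names its own finding and gives a fitting example. In 7.3.3 the example fits the kidney but the finding named does not. Exceptions that name something outside their own trigger: 1 of 4.

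**Does other text supply the renal exception?**

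- 7.1 lets Grade 1 or 2 events continue on protocol, but takes creatinine and clearance changes out of that rule and refers them to the specific section. For those grades 7.3.3 governs.
- 7.2 has a generic exception, available when the clinician "has compelling evidence that the adverse event is NOT due to PTX, dosing may continue". It applies only to Grade 3 or 4 events. The grading table is not reproduced in the protocol, so how the 7.3.3 thresholds map to grades cannot be read from the document.
- The introduction to section 7 gives clinical management decisions to the principal investigator together with the primary caregiver. It states no renal exception.
- Section 3.3 ties study discontinuation and dose reduction to events likely or thought to be related to study drug, and the criteria for study discontinuation list drug-related toxicity with a reference back to section 7. Both support the general principle of attribution. Neither restates or corrects the 7.3.3 condition.

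The mismatch therefore stands in current, operative text.

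**The case against.** The strongest reply is that this is a proofreading slip that would mislead nobody. The heading, the trigger, the nephritis work-up and the dehydration example are all renal, and an ALT rise has no antecedent anywhere in 7.3.3, so a reader would see the slip at once. Continuing drug after a renal decline on the strength of liver-test evidence would mean ignoring all of that. This stands: the second literal consequence is remote.

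It can also be said that the exception has little work to do. The trigger already requires a decline that is confirmed and not reversible, and dehydration, the one example given, would ordinarily be reversible and so would not reach the trigger. With 26 participants, about 8 weeks of treatment and clearance below 50 mL/min excluded at entry, qualifying cases should be few. Where one does occur, the usual literal result is to stop PTX, which is cautious. This also stands.

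Finally, sections 3.3 and 7.2, the introduction to section 7 and the discontinuation criteria all reflect the principle that attribution to study drug matters. That narrows the practical gap to renal declines below Grade 3. It does not close the gap, because 7.1 sends those events to 7.3.3 and the condition written there is the wrong one.

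These points limit the consequence. None of them shows that ALT was intended.

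**Conclusion.** The concern holds as a minor wording error in an operative safety rule. One of the four exceptions in 7.3, the one in 7.3.3, is conditioned on a test that plays no part in its trigger, and no other section corrects it. The carry-over from 7.3.2 is an inference from the matching wording; the mismatch itself is plain on the page and does not depend on that inference.

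The practical risk is small and the renal intent is clear. No effect on the sample size, the primary analysis or any stated figure is claimed. The reason to correct it is that either of two clinicians may invoke the clause to decide on permanent discontinuation, and they should not have to amend it silently or risk a recorded deviation for applying what was meant.

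**What to change.** In the exception in 7.3.3, replace the reference to a rise in serum ALT with *rise in serum creatinine/decrease in calculated creatinine clearance*, which agrees with the section's heading and with the way 7.1 refers to these events. Leave the triggers, the one-week limit on the pause and the dehydration example as they are.

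The cost is one phrase in the protocol. Design, sample size and analysis are unchanged.

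While the text is open, the authors could also consider whether the exception in 7.3.2 should name AST and total bilirubin beside ALT, since all three are triggers there. That is a separate, optional tidy-up.

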7.3.4 Rash

For a Grade 1 rash, management of PTX is at the discretion of the principal investigator and the primary caregiver.

For a Grade 2 rash, the principal investigator and primary caregiver will hold PTX until rash is resolved. At that time, the subject can be rechallenged at the same PTX dose. However, if the primary investigator or primary caregiver has compelling evidence that the rash is NOT due to PTX (e.g. sunburn), dosing may continue with no more than a one week hiatus at the discretion of the primary investigator or primary caregiver. Rescheduling of a main study visit, if necessary, will be at the discretion of the primary investigator.

If a Grade 2 rash recurs within one week, or if a Grade 3 or 4 rash occurs at any time, then PTX will be permanently discontinued.

